13.4 Inevaluable patients

If a patient fails to complete Radiation Therapy for reasons other than toxicity, the patient will be regarded as unevaluable.

### 13.5 Ineligible

A patient is deemed *ineligible* if after registration, it is determined that at the time of registration, the patient did not satisfy each and every eligibility criterion for study entry. If the patient receives treatment, the patient may continue treatment at the discretion of the physician as long as there are not safety concerns. The patient will continue in the Active Monitoring/Treatment phase of the study, as per **Section 4.0** of the protocol.

- - If the patient never received treatment, on-study material must be submitted. Survival Follow-up will be required per **Section 4.1** of the protocol.

### 13.6 Major Violation

A patient is deemed a *major violation*, if protocol requirements regarding treatment in cycle 1 of the initial therapy are severely violated that evaluability for primary end point is questionable. If the patient receives treatment, the patient may continue treatment at the discretion of the physician as long as there are no safety concerns. The patient will continue in the Active Monitoring/Treatment phase of the study, as per **Section 4.0** of the protocol.

### 13.7 Cancel

A patient is deemed a *cancel* if he/she is removed from the study for any reason before any study treatment is given. On-study material and the End of Protocol Treatment/Intervention must be submitted. No further data submission is necessary.

## **14.0 Body Fluid Biospecimens**

None

## **15.0 Drug/Device Information**

None

## **16.0** **Statistical Considerations and Methodology**

16.1 Study Design

The study is designed as a two arm 1:1 randomized Phase II trial with a total evaluable sample size of 102 patients (51 patients per arm) to evaluate an intermediate dose of 9 Gy (delivered over 3 fractions) or similar dose as described versus the standard of care (SOC) 24 Gy in 12 fractions for patients with indolent lymphoma, while simultaneously evaluating prognostic value of pre-radiation functional imaging parameters and molecular characteristics to predict treatment response and failure.

### 16.2 Primary endpoints

The following definition is used for the primary endpoint of interest:

- Acute toxicity: any adverse event grade 2 or higher (CTCAE v5.0) possibly related to radiation treatment, reported at End of Treatment, Day 7 post RT, or Day 14 post RT. Acute toxicity is reported as a proportion calculated as the number of patients with acute toxicity divided by the total number of treated patients.

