## **13.0 Treatment/Follow-up Decision at Evaluation of Patient**

13.1 Those patients who will not receive any radiation treatment or who will receive radiation treatment elsewhere will go off study per **Section 13.7**.

13.2 Patient who are CR, PR, or SD will continue to obtain PET or CT scans at each clinically indicated follow up for up to 24 months after the completion of radiation treatment.

13.3 Patients who develop PD or withdraw from further follow up assessments will be followed for event monitoring only per **Section 4.0**.

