### 16.3 Secondary

The following definitions are used for the secondary endpoints of interest:

• Response rate at 3 months post radiation treatment: is reported as a proportion calculated as the number of cases with complete response (CR) or a partial response (PR) at 3-month post radiation imaging based on Lugano criteria divided by the total number of treated patients. Treated patients who do not have a 3-month evaluation will be classified as a non-response.

• Local control rate at 2-years: defined from the time of registration to local relapse that overlaps the treated site (95% isodose line).

• Patient Reported Outcomes/Quality of life: FACIT-Fatigue given as SOC for Lymphoma patients within 3 months after end of radiation treatment will be used as outlined in section 4.0 and 7.0.

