### 16.5 Statistical Design

16.5.1 Decision Rules

16.5.1.1 A two group χ^2^ test of equal proportions in acute adverse events will be conducted to determine the efficacy in acute toxicity reduction within the treatment arm. If the p-value of the statistical test is less than 0.10 then the treatments will be considered significantly different in the direction of the point estimates. Therefore, a significant difference in the direction of the experimental arm will deem the treatment favorable and worth consideration in future trials. If the test is non-significant then the experimental arm will not be considered significantly different in toxicity profile and therefore, not considered for future trials. It is also important to consider the local control rate when deciding whether to pursue further study. In the FoRT trial, the 2-year local progression-free rate was 94.1% after 24 Gy and 79.8% after 4 Gy. If the observed 2-year probability of local control is more than 7% inferior with 9 Gy versus 24 Gy, then we will not consider future trials. For example, if the 2-year local control rate is 94.1% after 24 Gy, and less than 87.1% after 9 Gy then we would not pursue further study.

16.5.1.2 Over Accrual: We will accrue approximately 10% over-accrual (112 total patients, 56 per arm) in order to ensure 102 evaluable patients as described in previous sections. The first 102 evaluable patients will be utilized for analysis of the primary endpoint.

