16.5.4 Power and Significance Levels

The study is designed as a two arm 1:1 randomized Phase II trial with a total evaluable sample size of 102 patients and a 1:1 randomization (51 patients per arm). We will utilize a two-group chi-squared test of equal proportions with a two-sided α = 0.10 to test the primary hypothesis given acute toxicity estimates observed in the FoRT trial (grade 2+ acute toxicity of approximately 31% in the 24 Gy arm and approximately 9% in the 4 Gy arm). We hypothesize similar estimates in the 24 Gy arm, and we hypothesize acute toxicity rates of 10% in the 9 Gy arm. With a two-sided alpha of 0.10 we will achieve 80% power to detect difference in proportions of 0.21 when the acute toxicity is assumed to be 0.31 in the standard of care arm and 0.10 in the experimental arm. To ensure evaluability of our primary endpoint we will accrue 10 additional patients (56 per arm) to account for approximately 10% lost to follow-up.

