16.6 Analysis Plan

The primary analysis for this trial will commence once the first 102 evaluable patients have completed their Day 14 Post ISRT visit. It is anticipated that the earliest date in which the results will be made available via a manuscript, abstract, or presentation format is when 102 patients have experienced an acute toxicity or 2 weeks post radiation therapy follow-up.

16.6.1 Primary Analysis: The primary analysis will be to compare the proportion of patients who experience an acute toxicity within the first 2 weeks of finishing RT between the 2 treatment arms.

16.6.1.1 Acute toxicity: All patients who were registered to the study and started treatment will be included in the acute toxicity analysis. Acute toxicity has been defined in section 16.2. A chi-squared test will be used to compare acute toxicity rates between treatment arms. A two-sided p-value less than 0.10 will be considered statistically significant (see decision rule). To assess the size of differences, absolute risk difference and relative risk will be calculated; 95% confidence intervals will be calculated using the score method. Although we will use an alpha of 0.10 for deciding whether to pursue further study, 95% confidence intervals will be reported for estimates for ease of interpretation.

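### The primary toxicity rate counts a treated patient with no acute assessment as toxicity-free, which conflicts with the plan's evaluable-patient rule and leaves evaluability unconnected to the toxicity assessments

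*Protocol*

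**What the plan says.** Protocol section 16.2 defines acute toxicity as a grade 2 or higher event, possibly related to radiation, "reported at End of Treatment, Day 7 post RT, or Day 14 post RT". It then fixes the rate: "Acute toxicity is reported as a proportion calculated as the number of patients with acute toxicity divided by the total number of treated patients". Section 16.6.1.1 repeats the denominator: "All patients who were registered to the study and started treatment will be included in the acute toxicity analysis".

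Other sections describe a different set. Section 16.5.1.2 states: "The first 102 evaluable patients will be utilized for analysis of the primary endpoint". Section 16.5.4 explains the extra accrual: "To ensure evaluability of our primary endpoint we will accrue 10 additional patients (56 per arm) to account for approximately 10% lost to follow-up". Section 16.6 starts the primary analysis once the first 102 evaluable patients have had their Day 14 visit. The only definition of an unevaluable patient, in section 13.4, is one who does not complete radiotherapy for reasons other than toxicity. It does not mention toxicity visits.

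For response, section 16.3 gives an explicit rule for missing assessments: "Treated patients who do not have a 3-month evaluation will be classified as a non-response". The primary endpoint has no matching sentence. Section 13.3 provides a route out of assessment: "Patients who develop PD or withdraw from further follow up assessments will be followed for event monitoring only".

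**The concern.** A treated patient with no acute assessment cannot add to the numerator but stays in the denominator, so the formula scores that patient as free of toxicity. For response, the plan gives a missing assessment the unfavourable score. For toxicity, the formula gives it the favourable one.

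A single two-sided test at 0.10 decides whether the reduced-dose arm is judged favourable (section 16.5.1.1). If more patients go unassessed in that arm, its toxicity looks lower than it is. If more go unassessed in the 24 Gy arm, a real difference is hidden. No blinding is described, and section 4.0 gives treatment times of about 5 and 16 days, so weekly contact during treatment yields more contacts in the 24 Gy arm. Equal ascertainment therefore cannot be taken for granted, although nothing in the protocol shows that it will be unequal.

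**Working it through.** **Inputs from the protocol (section 16.5.4):** 51 evaluable per arm, 56 accrued per arm, true rates 0.31 (24 Gy) and 0.10 (experimental), chi-squared test, two-sided alpha 0.10, stated power 80%.

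**Assumptions:** the share m of treated patients with no captured acute assessment is 0% to 20% per arm, and missingness is unrelated to toxicity within an arm. The protocol gives no figure for m by arm.

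**1. The plan's own figure.** With mean rate p̄ = (0.31 + 0.10)/2 = 0.205, the normal approximation is

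power = Φ{ [0.21·√51 − 1.645·√(2·0.205·0.795)] / √(0.31·0.69 + 0.10·0.90) } = Φ{ (1.500 − 0.939)/0.551 } = Φ(1.017) = 84.5%.

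Summing the two binomial distributions exactly gives 85.8% for the uncorrected chi-squared test, and 79.1% for both the continuity-corrected test and Fisher's exact test. The stated 80% is therefore reproduced to within a point by a corrected or exact calculation. The exact uncorrected test is used below.

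**2. Effect of the scoring rule.** If unassessed patients count as non-events, the observed rate is p·(1 − m).

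| Loss, 24 Gy / experimental | Observed rates | Difference | Power, 51 per arm | Power, 56 per arm |
|---|---|---|---|---|
| 0% / 0% | 31.0% v 10.0% | 21.0 points | 85.8% | 88.2% |
| 10% / 10% | 27.9% v 9.0% | 18.9 points | 81.2% | 84.2% |
| 15% / 5% | 26.35% v 9.5% | 16.85 points | 73.2% | 76.6% |

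For the second row: 0.31 × 0.9 = 0.279, 0.10 × 0.9 = 0.090, and 0.279 − 0.090 = 0.189.

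**3. Comparison with leaving unassessed patients out.** At 10% loss, 51 × 0.9 ≈ 46 per arm remain. The rates stay at 31% and 10%, and exact power is 83.1%, against 81.2% when missing is scored as no toxicity.

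**4. Chance of a false result favouring the experimental arm** (equal true rates, 51 per arm):

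| True rate in both arms | No loss | 15% experimental, 5% control | 20% experimental, 0% control |
|---|---|---|---|
| 31% | 5.2% | 10.0% | 17.6% |
| 20% | 5.1% | 8.3% | 13.0% |
| 10% | 5.2% | 7.5% | 10.2% |

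With 10% lost in both arms and a true rate of 31%, the figure is 5.2%, the same as with no loss.

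**5. Does the evaluability wording remove the problem?** A patient who completes radiotherapy and then has no toxicity assessment is not unevaluable under section 13.4. That patient is also in the set of sections 16.2 and 16.6.1.1. Only if evaluable is taken to mean that the Day 14 visit was done does the patient drop out, and no definition says so.

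**The case against.** - **The evaluable set may govern.** If the primary analysis uses the first 102 evaluable patients, all with Day 14 completed, the problem does not arise. This stands in part: the scoring rule is not settled, because the sections disagree. But the Day 14 sentence in section 16.6 sets the timing of the analysis and does not define evaluability.
- **Events can be captured in other ways.** Section 7.2.1 requires weekly contact, by phone if needed, during treatment and for two weeks after. Section 10.2.1.1 collects events from any source, with onset dates, to 30 days. Sections 2.1 and 7.2.3 define the outcome by occurrence within 14 days. This stands. A reader might infer that anyone who misses a visit is scored toxicity-free. The documents do not support that, because an event reported at another visit still counts and other contact may establish the rest.
- **The 10% is not a rate of unassessed patients.** Section 16.5.2 assigns the same 10 patients to ineligibility, cancellation, major treatment violation and other reasons, and under section 13.7 cancelled patients are never treated. This stands, so 10% is used here only as an assumption.
- **Unequal loss is hypothetical.** This stands too. The imbalances are illustrations, and no section predicts one or its direction.
- **Missing-data methods belong in the SAP.** That is fair for the choice of method, and imputation need not be required here. It does not cover the endpoint formula, which the protocol fixes and which conflicts with its own evaluability rule.

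**Conclusion.** The point holds in a limited form. Sections 16.2 and 16.6.1.1 score an unascertained treated patient as toxicity-free, sections 16.5.1.2 and 16.5.4 imply a different set, and section 13.4 does not settle the matter.

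Equal loss costs little: 2.1 points of difference and 4.6 points of power at 51 per arm, under an assumed 10% loss. Power still exceeds the stated 80%, and the false-favourable rate does not change. It would be tempting to conclude that the trial is underpowered or tilted towards the experimental arm, but the documents do not support either. The real exposure is unequal loss, where the false-favourable rate could roughly double (10.0%) or more than triple (17.6%) under the assumed imbalances with both true rates at 31%. The increase is smaller at lower true rates. These figures assume complete non-ascertainment; partial loss would do less.

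**What to change.** In sections 16.2, 16.5.1.2 and 16.6.1.1:

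1. Name one primary analysis set and use it throughout.
2. Count a patient with a reported qualifying event as an event, whichever visits were missed.
3. Count a treated patient as having no acute toxicity only if status through Day 14 is established, at a visit or by other contact using onset dates. Treat all others as missing.
4. Report the number missing by arm.
5. Add a sensitivity analysis over all treated patients that scores missing as toxicity in the experimental arm and as no toxicity in the 24 Gy arm.

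This takes a few sentences and no new visits or patients. A few patients leave the primary comparison and intervals widen slightly. Keeping partly followed patients who had events while setting aside those who did not may raise the rates a little. The count of missing patients by arm will show whether that matters.

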### 16.3 Secondary

The following definitions are used for the secondary endpoints of interest:

• Response rate at 3 months post radiation treatment: is reported as a proportion calculated as the number of cases with complete response (CR) or a partial response (PR) at 3-month post radiation imaging based on Lugano criteria divided by the total number of treated patients. Treated patients who do not have a 3-month evaluation will be classified as a non-response.

• Local control rate at 2-years: defined from the time of registration to local relapse that overlaps the treated site (95% isodose line).

• Patient Reported Outcomes/Quality of life: FACIT-Fatigue given as SOC for Lymphoma patients within 3 months after end of radiation treatment will be used as outlined in section 4.0 and 7.0.

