### 2.2 Secondary Goals

The secondary objectives of the study are to evaluate:

- Patient Reported Quality of life [timeframe: 7 days after radiation treatment end date]
- Response rate [timeframe: at 3 months (+/- 14 days) post radiation treatment start date]
- Local control rate [timeframe: up to 24 months after the completion of radiation treatment]
- Relapse-free survival [timeframe: up to 24 months after completion of radiation treatment]

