#### 3.1.3 Any stage disease

#### 3.1.4 Initial, refractory, or relapsed disease. If relapse involves the site to be treated there must be evidence of disease progression

#### 3.1.5 ECOG Performance Status (PS) ≤3 (Appendix I)

#### 3.1.6 Negative pregnancy test done ≤7 days prior to registration, for persons of childbearing potential only

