7.2.3 Outcomes

- Adverse events (CTCAE version 5.0) will be assessed at Baseline, End of Treatment, Day 7 post-RT, Day 14 post-RT, and at 3 months within the windows defined in **Section 4.0**. The primary outcome is acute toxicity, defined as any adverse event grade 2 or higher at least possibly related to radiation treatment that occurs up to 14 days after the end of radiation treatment.
- Patient reported outcomes (FACIT-Fatigue scale) will be collected at Baseline, End of Treatment, Day 7 post-RT and 3 months post-RT within the windows defined in **Section 4.0**.
- Financial toxicity, determined by the COST-FACIT QOL, will be evaluated after RT at the end of treatment (+/- 1 day).
- Financial health care expenditure (see **Section 7.2.8**) will be collected after RT at the end of treatment.
- Response rate will be obtained during follow-up imaging and clinical exam at 3 months (+/- 14 days) post radiation treatment.
- Local recurrence rate will be obtained during follow-up imaging and clinical exam at 3 months, 6 months, 12 months, 18 months, and 24 months post radiation treatment within the windows defined in **Section 4.0**.
- Overall survival will be assessed during follow-up at 3 months, 6 months, 12 months, 18 months, and 24 months post radiation treatment per clinician's discretion within the windows defined in **Section 4.0**.

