11.4 Response assessment

Schedule of evaluations: All patients are required to receive a PET/CT scan at baseline. Post-treatment tumor recurrence will be monitored with follow-up PET/ CT scans to assess tumor response based on Lugano criteria until local progression within radiation field or death (or up to 24 months after the completion of radiation treatment) at which point participants will go to survival follow-up. Patients who did not test FDG negative at baseline are strongly recommended to receive a PET/CT or CT if PET/CT is not done, 3 months after treatment as part of post-treatment follow-up. Patients will receive a follow-up CT scan at 6 months post-treatment and will continue to do so every 6 months at clinician’s discretion. For patients without measurable disease on baseline PET/CT or CT (eg cutaneous lymphoma) follow up imaging is not required and response will be based on clinical exam.

Patients with gastric lymphoma will receive an endoscopy prior to registration. Post-treatment tumor recurrence will be monitored with follow-up endoscopies at 3 months and every 6 months per clinician’s discretion after treatment.

The Lugano criteria is outlined in Appendix III. For gastric lymphoma, additional information regarding pathologic response will be provided via endoscopy.

[figure not shown]

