## Table from Olsen *et al* see reference 17.

## **12.0 Descriptive Factors**

• Age (≤60 years and >60 years)

• Sex (M/F/Unknown/Intersex)

• Diagnosis/Histology (Follicular I/II, Follicular IIIA, Marginal Zone/Malt, Other)

• Reason for radiotherapy (curative/palliative)

• Eastern Cooperative Oncology Group (ECOG) performance status (0, 1, 2 vs. 3)

• Ann Arbor stage (Stage I/II vs. III/IV/relapse/refractory)

• Target site maximum diameter (>6 cm vs. ≤6 cm)

• Lactate dehydrogenase at registration/first treatment (≤ULN vs. >ULN)

• Extranodal site (yes/no)

• Previous radiation therapy (yes/no)

• Previous chemotherapy (yes/no)

• Number of sites treated in this trial (≤2 or >2)

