16.6.2 Secondary Analyses

16.6.2.1 Response Rate: All patients who were registered to the study and started treatment will be included in the response rate analysis. Response rate will be defined as the proportion of patients displaying response (PR or CR) at 3 months post treatment; patients who did not have a 3-month post treatment assessment will be considered a non-response. A chi-square test will be used to compare response rates between the two treatment arms. Absolute risk difference and relative risk will be calculated; 95% confidence intervals will be calculated using the score method.

16.6.2.2 Local control: All patients who were registered to the study and started treatment will be included in the local control analysis. A local recurrence event is any event defined as disease relapse occurring in the area treated before with radiation (anything included within the 95% isodose line). The local control interval will be defined as the number of days from end of radiation treatment until first local recurrence within 24 months post radiation treatment; censoring will occur at date of patient death or date of last disease evaluation (based on imaging and clinical exam). Local control rates will be estimated separately for the two treatment groups at 3-, 6-, 12-, 18, and 24-months post radiation treatment using the Kaplan-Meier method. Hazard ratio and 95% confidence interval for comparison of local recurrence between the two treatment arms will be estimated from a Cox proportional hazards model.

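### The 3-month response endpoint is not limited to irradiated lesions in an any-stage population given involved-site radiation, and its imaging-based numerator contradicts the sections that waive imaging

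*Protocol*

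**What the plan says.** **Definition.** Section 16.3 takes the "number of cases with complete response (CR) or a partial response (PR) at 3-month post radiation imaging based on Lugano criteria" and divides by all treated patients. It adds: "Treated patients who do not have a 3-month evaluation will be classified as a non-response". Section 16.6.2.1 analyses CR or PR over all registered patients who started treatment, with a chi-square test, risk difference and relative risk. It has its own default: "patients who did not have a 3-month post treatment assessment will be considered a non-response".

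**Population and treatment.** Section 3.1.3 admits "Any stage disease" and section 3.1.4 admits initial, refractory or relapsed disease. Section 5.0 makes Stage III/IV/relapse/refractory one stratum, and section 12.0 records curative or palliative intent. Section 7.1.1 specifies involved-site radiation.

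**Assessment.** Section 7.2.3 states: "Response rate will be obtained during follow-up imaging and clinical exam at 3 months (+/- 14 days) post radiation treatment". Section 4.0 (footnote 7) and section 7.2.2 do not require follow-up imaging for primary cutaneous lymphoma or for disease not measurable at baseline. For the latter, section 11.4 says "follow up imaging is not required and response will be based on clinical exam". Footnote 6 of section 4.0 gives the 3-month endoscopy ±30 days.

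**The concern.** Elsewhere the protocol separates treated from untreated disease. Local control is tied to the 95% isodose line (16.3, 16.6.2.2), and failure is classed as local or distant by the same line (11.3). The PET metrics of section 2.4.2 are computed on the sites to be irradiated. Response carries no such limit in the visible text.

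Untreated disease says nothing about whether the dose delivered in the field was enough. If it can turn an in-field responder into a non-responder in both arms, the arms look more alike than they are where the dose was given. In a trial that lowers the dose, that error hides a loss of efficacy. Section 2.4.2 would also pair a treated-site predictor with a whole-patient outcome.

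The second problem is a contradiction. Section 16.3 admits to the numerator only responses seen on imaging by Lugano, while other sections waive imaging for some patients and use clinical exam instead.

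**Working it through.** The protocol gives no expected response rate and no power for response, so there is no figure to reproduce. The calculation below illustrates direction and possible size.

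**1. Dilution.** Inputs:
- n = 51 evaluable per arm (section 16.1).
- p, the in-field response: 0.95 v 0.80 (assumed).
- f, the share of patients with unirradiated disease: 0.25 to 0.50 (assumed, equal in both arms).
- k, the share of their in-field responders who still reach whole-patient CR/PR: 0.2 to 0.5 (assumed, equal in both arms).

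Whole-patient rate = (1 − f)p + fkp = p[1 − f(1 − k)]. Unpooled z = (p1 − p2) / √{[p1(1 − p1) + p2(1 − p2)]/n}.

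In-field: 0.15 / √[(0.0475 + 0.1600)/51] = 0.15/0.0638 = 2.35.

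| f | k | factor 1 − f(1 − k) | rates | difference (points) | z |
|---|---|---|---|---|---|
| 0.25 | 0.5 | 0.875 | 83.1% v 70.0% | 13.1 | 1.58 |
| 0.25 | 0.2 | 0.80 | 76.0% v 64.0% | 12.0 | 1.33 |
| 0.40 | 0.5 | 0.80 | 76.0% v 64.0% | 12.0 | 1.33 |
| 0.40 | 0.2 | 0.68 | 64.6% v 54.4% | 10.2 | 1.05 |
| 0.50 | 0.5 | 0.75 | 71.3% v 60.0% | 11.3 | 1.20 |
| 0.50 | 0.2 | 0.60 | 57.0% v 48.0% | 9.0 | 0.91 |

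The factor multiplies both arms, so the risk difference shrinks by it. The relative risk stays at 0.80/0.95 = 0.84 under this model.

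A second illustration assumes 0.90 v 0.75 in the field, two-sided alpha 0.05, and a share of both arms scored as non-response whatever happens in the field. Power is 51% with a share of 0, 34% at 10%, 25% at 20% and 19% at 30%. Response is weakly powered even before dilution.

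**2. Imaging.** Three texts bear on patients exempt from imaging:
- The 16.3 numerator needs 3-month imaging read by Lugano.
- Section 11.4 and footnote 7 use clinical or physical exam for response.
- The non-response defaults turn on a missing evaluation (16.3) or assessment (16.6.2.1), not on missing imaging.

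Read literally, 16.3 keeps exempt patients in the denominator with no route into the numerator. Read with 11.4, they can be responders. Both readings cannot stand.

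**3. Windows.** Take 3 months as 91 days and count both windows from the same day. Section 2.2 counts response from the start of radiation and the other sections count post treatment; that difference is set aside here. Response: days 77 to 105, 29 days. Endoscopy: days 61 to 121, 61 days. Permitted endoscopy days outside the response window: 61 − 29 = 32, or 32/61 = 52%, on both sides.

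**The case against.** **Appendix III is not shown.** Section 11.4 refers to it for the criteria, so a treated-site limit could be there. This stands as a caveat. None appears in 16.3, 16.6.2.1 or the text of 11.4.

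**The size rests on invented inputs.** This stands. The protocol gives neither in-field response rates nor the share with unirradiated disease. A reader might take the stratification factor as evidence of a large share, but that stratum includes relapsed or refractory disease that may be localised and wholly irradiated, and its size is not stated. Even z = 2.35 is only about 65% power at two-sided 0.05, so it would be wrong to say that a loss sure to be detected is missed.

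**Response decides nothing.** The efficacy criterion in 16.5.1.1 is 2-year local control with a 7-point margin, and local control is already restricted to the field. This stands and limits the importance of the point.

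**Exempt and gastric patients are not necessarily misclassified.** A reader might infer that they are. The documents do not support it: clinical exam can supply the evaluation, section 11.4 makes endoscopy supplementary information on pathologic response, and 3-month PET/CT or CT stays scheduled for gastric patients. No text discards an endoscopy done outside ±14 days. What remains is conflicting wording and no rule for combining pathology with Lugano.

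**Relapse-free survival.** A reader might extend the criticism to the goal listed in 2.2 as "Relapse-free survival [timeframe: up to 24 months after completion of radiation treatment". The protocol gives it no event definition or time origin, so there is no definition to fault.

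**The PET pairing is partial.** Section 2.4.2 names the treated sites, but 16.4.2 refers more loosely to the patients' disease.

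**Conclusion.** The point holds for the response endpoint. On the visible text, response is a whole-patient CR/PR in a population that can carry disease outside the field, so that disease can decide the outcome. The direction is clear if such disease is spread equally over the arms and acts independently of dose: the absolute difference shrinks. The amount cannot be stated from the documents. The fall from 15 points to 9 to 13 is an illustration on assumed values.

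The imaging wording in 16.3 contradicts 4.0, 7.2.2 and 11.4, and the endoscopy and response windows differ. These are inconsistencies to reconcile, not shown misclassification. This is a secondary endpoint: the primary toxicity test and the local control decision rule do not change.

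**What to change.** - In 16.3 and 16.6.2.1, define the secondary endpoint as response of the irradiated site(s), assessed by the modality the protocol already assigns: PET/CT or CT, and clinical exam where imaging is waived. Keep all treated patients in the denominator.
- Report whole-patient Lugano response descriptively.
- Reconcile the imaging wording of 16.3 with 11.4, footnote 7 and 7.2.2.
- Reconcile the endoscopy and response windows with each other, and state how endoscopic pathology enters the response call.
- If Appendix III already limits response to treated sites, say so in 16.3.

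The cost is protocol wording and one CRF field for treated-site response, using the same scans, exams and endoscopies. The downside is that the main response rate becomes less comparable with whole-body Lugano rates, which the descriptive line partly offsets.
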